### Data collection and study outcomes

Data will be collected from participants at baseline and 6-months online. In addition, for safety the eating disorder screening will be conducted at 2-months and 4-months for all participants. The co-primary outcomes, secondary outcomes and their assessments are provided below in Table 1. Multiple endpoints have been selected such that a significant effect against either one may be taken as evidence of efficacy. The co-primary outcomes are change in moderate-to-vigorous minutes of physical activity (MVPA) minutes per day and change in the proportion of participants meeting vegetable intake guidelines (> 3 serves per day). MVPA will be measured by ActivInsights Geneactiv wrist-worn accelerometers [46]. After enrolment and at the 6-month assessment, participants will be mailed an accelerometer to wear for 7 days and then return by pre-paid post to the research team. Vegetable intake will be measured using data from the Australian Child and Adolescent Eating Survey (ACAES), developed by the University of Newcastle [44].

**Table 1 Tab1:** Description of Health4Me study outcomes and assessments

Outcome	Assessment
*Dual Primary Outcomes*	
Vegetable intake	Australian Child and Adolescent Eating Survey [ACAES] [44, 45]
Moderate-vigorous physical activity (MVPA) min/day	Geneactiv activity and sleep unit worn for 7 days [46]
*Secondary Outcomes*	
BMI^a^ z-score	Units BMI is above or below average for the age- and sex-specific reference values, using participant self-reported weight and height [47]
Waist-to-height ratio	Mid measure between the iliac crest and lowest rib and height, using participant self-reported waist circumference and height [47]
Dietary quality	Australian Child and Adolescent Eating Survey [ACAES] [44, 45]
Sleep quality	Pittsburgh Sleep Quality Index Short [PSQI-Short] [48, 49]
Health-related quality of life	Child Health Utility instrument [CHU9D] [50]
Self-efficacy	Self-efficacy for Healthy Eating and Physical Activity [SE-HEPA] [51]
Anxiety	General Anxiety Disorder-7 [GAD-7] [52]
Depression	Centre for Epidemiological Studies Depression Scale Revised-10 [CESDR-10] [53]
Psychological distress	Kessler Psychological Distress Scale [K6] [54]
Eating disorder risk	InsideOut Institute screening tool [IOI-S] [55]
Food insecurity	USDA^b^ 6-item food security module [56]
eHealth literacy	eHEALS eHealth Literacy Scale [57]

^a^*BMI* Body mass index

^b^*USDA* United States Department of Agriculture

Weight, height and waist circumference will be self-reported by participants according to a standardised digital protocol [47]. Participants will be shown how to correctly measure weight, height and waist circumference by videos put together by the research team and embedded into the data collection form. Self-reported height and weight has been validated amongst young adults in an Australian population [58–60]. Weight, height and waist circumference measurements will be used to calculate BMI z-score (using age and sex specific reference values) and waist-to-height ratio.

The following questionnaire-based assessments have demonstrated reliability and validity in adolescent populations and will be completed online at baseline and follow-up assessments. Sleep quality will be measured using the Pittsburgh Sleep Quality Index-Short [48, 49]. Health related quality of life and self-efficacy will be measured by the Child Health Utility Instrument (CHU9D) [50] and Self Efficacy for Healthy Eating and Physical Activity (SE-HEPA) [51] respectively. Anxiety, Depression and Psychological Distress will be measured by the General Anxiety Disorder-7 (GAD-7) [52], Centre for Epidemiological Studies Depression Scale Revised-10 (CESDR-10) [53] and the Kessler Psychological Distress Scale (K6) [54]. Eating disorder risk will be measured using the InsideOut Institute screening tool (IOI-S) [55]. Food insecurity will be measured with the USDA 6-item food security module [56] and eHealth literacy with eHEALS eHealth Literacy Scale [57]. A schedule of enrolment, interventions and assessments is presented in Table 2. All data will be entered electronically into Research Electronic Data Capture (REDCap), hosted on secure servers by the University of Sydney. Electronic data will be monitored by the research team through monthly reports to ensure quality and completeness of the data.

**Table 2 Tab2:** Health4Me study schedule of enrolment and assessments

Assessments	Pre-baseline	Baseline	6-month follow-up

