### Randomization and blinding

Participants will be randomly allocated to either the intervention or control group. The control group will receive usual care (no intervention). Participants will view digital advertisements for the study on social media, after clicking on a link it will take them to the participant information sheet which they can read and provide informed e-consent. After obtaining electronic consent from adolescents (and their parents or guardians if < 14 years old) and completing the baseline assessment on a secure web-based database, a member of the research team will randomize the participant via a centralized, computerized randomisation program in a uniform 1:1 allocation ratio (intervention: control). Randomization is based on both permuted blocks with randomized block sizes and stratification, where the strata are age and gender. A randomization list will be generated by an independent statistician. Members of the research team who enrol and conduct follow-ups with participants will be blinded to group allocation.

For each participant, the randomization program automatically produces a study identification number. On the following Monday after the baseline assessment, the computer system automatically sends the assigned text message program to the participant. Therefore, the random allocation sequence will be concealed from study personnel at baseline and at 6-months. Participants will be encouraged not to discuss whether they are or are not receiving the text messages until the end of the 6-month follow-up.

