### Statistical considerations

For the outcome of MVPA (minutes per day), 312 (156 per group) participants are needed to achieve 90% power to observe the mean difference of 14.8 (control: 42.55 and intervention: 57.36) with standard deviations (SD) of 21.45 for control and 37.79 for intervention and accounting for 30% dropout. A two-sided two-sample unequal-variance t-test was used. The Bonferroni adjusted significance level of 0.025 was used to account for two primary outcomes. To detect a difference in vegetable intake at 6-months, 390 (195 per group) participants will achieve 90% power to detect 13.37% difference in the proportion of appropriate vegetable consumption (control: 4.85% and intervention: 18.22%) and accounting for 30% dropout [61]. The two-sided Z-Test with unpooled variance was used with the significance level of the test is 0.025. Therefore, a sample size of 390 will allow the detection of the change in MVPA or vegetable intake.

All statistical analyses will follow a pre-specified statistical analysis plan guided by our team statistician. Analyses of the primary and secondary outcomes will be conducted according to the intention-to-treat principle. Continuous outcomes at 6-months will be analysed using analysis of covariance (ANCOVA), and categorical outcomes at 6-months will be analysed using log-binomial regression, adjusting for the outcome values at baseline. Planned subgroup analyses will investigate interactions between treatment and subgroups, including categories of age, socioeconomic status and ethnicity, to explore trends for scale up. All tests will be two-sided with a significance level of 0.05. Analyses of the two primary outcomes will be controlled for the family-wise error rate using Holm correction [62]. No multiplicity adjustments will be performed for secondary outcomes as they are exploratory analyses. The analyses will be performed using SAS (V9.4 SAS Institute Inc. Cary NC, USA).

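### As most naturally read, the protocol has the baseline accelerometer worn after randomisation and into the first messages; the sequence must be fixed because it can bias the MVPA co-primary result

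*Protocol article*

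**What the plan says.** Four parts of the protocol article bear on the order of events.

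- **Randomization and blinding.** Allocation comes after consent and the web baseline: "completing the baseline assessment on a secure web-based database, a member of the research team will randomize the participant". The start of the programme is tied to that same assessment: "On the following Monday after the baseline assessment, the computer system automatically sends the assigned text message program to the participant".
- **Data collection and study outcomes.** Baseline and 6-month data are described as gathered over the internet: "Data will be collected from participants at baseline and 6-months online". The accelerometer is handled separately: "After enrolment and at the 6-month assessment, participants will be mailed an accelerometer to wear for 7 days and then return by pre-paid post". The endpoint is defined as a change: "The co-primary outcomes are change in moderate-to-vigorous minutes of physical activity (MVPA) minutes per day".
- **Table 2.** Eligibility screening and consent sit under the Enrolment heading in the pre-baseline column. Randomisation sits under the same heading in the baseline column. Physical activity is listed as a baseline assessment.
- **Statistical considerations.** "Continuous outcomes at 6-months will be analysed using analysis of covariance (ANCOVA"), with the model "adjusting for the outcome values at baseline".

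Nowhere is completed wear, or return of the device, made a condition for randomisation or for the automatic first message.

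**The concern.** A baseline covariate is safe to adjust for because treatment cannot have influenced it. Here the value that serves as baseline for a co-primary outcome appears to be collected after allocation and while messages are arriving. Physical activity is one of the topics of those messages, and participants know whether they are receiving them. If activity in the intervention arm has already shifted during the wear week, part of the treatment effect is recorded as baseline and then subtracted, fully in a change score and partly in ANCOVA. The trial could not afterwards separate an early response from a true starting level. A baseline week that has been missed cannot be collected later.

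**Working it through.** **1. The plan's own figure.** Inputs, from Statistical considerations: "mean difference of 14.8 (control: 42.55 and intervention: 57.36"), so the difference is 57.36 - 42.55 = 14.81 min/day; SDs 21.45 and 37.79; two-sided alpha 0.025; 90% power; 30% dropout. The unequal-variance t-test needs 109 per arm (power 0.902). Then 109 / 0.70 = 155.7, rounded up to 156 per arm or 312 in total, as stated. The planned effect of 14.81 min/day is therefore a sound yardstick for the bias.

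**2. The calendar.** Call the day the web baseline is completed day 0 and assume the device is posted that day. The first-message Monday falls between day 1 (baseline on a Sunday) and day 7 (baseline on a Monday). With a posting delay of d days, the wear days are d+1 to d+7. The delays below are assumptions; the documents give none.

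| Posting delay d (days) | Wear days, of 7, on or after the first-message Monday |
|---|---|
| 0 | 1 to 7 |
| 1 | 2 to 7 |
| 2 | 3 to 7 |
| 3 | 4 to 7 |
| 5 | 6 to 7 |

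The range in each row runs over the weekday on which the baseline is completed. Even with no delay, at least one wear day overlaps. With one day of posting, the last wear day is day 8, against a first message no later than day 7.

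**3. The bias, if there is overlap.** Let e be the between-arm difference in MVPA already present in the baseline wear week, and b the ANCOVA slope on baseline.

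- ANCOVA: bias = -b × e
- Change score: bias = -e

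A simulation with b = 0.5 and e = 25% of 14.81 (3.70 min/day) gave an adjusted effect of 12.95. The formula gives 14.81 - 0.5 × 3.70 = 12.96.

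The documents give neither b nor e. ANCOVA bias in min/day over an assumed range:

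| Slope b | e = 0 | e = 10% (1.48) | e = 25% (3.70) | e = 50% (7.41) |
|---|---|---|---|---|
| 0.3 | 0 | -0.44 | -1.11 | -2.22 |
| 0.5 | 0 | -0.74 | -1.85 | -3.70 |
| 0.7 | 0 | -1.04 | -2.59 | -5.18 |

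As a low-end reference, if the effect built up evenly over 26 weeks (also an assumption), the first-week shift would be 14.81 / 26 = 0.57 min/day. The bias at b = 0.5 would then be 0.5 × 0.57, or about -0.28 min/day.

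**4. After the fix.** With wear finished before allocation, e has expectation zero. The target stays at 14.81 min/day and the 312 is unchanged.

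**The case against.** **The order is inferred.** No sentence says that baseline wear follows randomisation. Table 2 puts consent under Enrolment in the pre-baseline column and physical activity in the baseline column. If enrolment means consent, and the baseline assessment includes the wear week, then wear precedes both allocation and the Monday trigger. This reading cannot be excluded. It is the weaker one, because the baseline assessment is described as completed on a web database, randomisation is itself listed under Enrolment, and nothing makes the trigger wait for the device.

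**Bias is not a certainty.** A reader might infer that adjusting for this baseline necessarily biases the result. It does not: a covariate measured after allocation but not yet affected by treatment leaves ANCOVA unbiased. A large early shift is also doubtful. The messages cover six topics and go out on four days a week, and any wear days before the first message dilute the shift. Attenuation from a beneficial early effect would not create false efficacy.

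**A power loss should not be quoted.** It is tempting to put reduced effects of 12.96 or 11.11 min/day into the planned test. At 330 participants with 30% dropout (115.5 per arm), that takes power from 92% to 83% or 69%. At 390 (136.5 per arm), it goes from 96% to 89% or 77%. These figures presuppose an early shift of 25% or 50%, which nothing in the documents supports. They also keep the unadjusted SDs while using a slope of 0.5 to generate the bias. If that slope reflects a correlation of 0.5, the residual SDs shrink by √0.75, and power is 92% or 82% at 330 and 96% or 88% at 390.

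**Missing baselines.** A reader might add that unreturned devices become baselines lost after randomisation, unequally by arm. How missing values are handled is normally left to the SAP, which is not shown, and nothing in the article indicates an imbalance.

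**Conclusion.** The point stands as a defect in the stated sequence with a conditional consequence. On the most natural reading, baseline MVPA is measured after allocation and overlaps the first messages; the overlap is then unavoidable by the calendar. The alternative reading remains open, so the sections must be reconciled. If wear does overlap, the bias in the adjusted effect is -(slope × e): from 0 to about -5.2 min/day for a slope of 0.3 to 0.7 and e from 0 to 50% of 14.81. It acts towards the null when the early effect is beneficial and vanishes when there is no early difference. Both inputs are assumptions, and no definite loss of power follows. The point still merits correction before recruitment proceeds, because it concerns a co-primary endpoint and the order of events is core design, not detail left to an analysis plan.

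**What to change.** State the order explicitly. Mail the device at consent, and specify that randomisation, or at minimum the first programme message, takes place only after the 7-day baseline wear has ended, for example on the Monday after the last wear day. Align Randomization and blinding, Data collection and study outcomes, and Table 2 with that rule. If wear already precedes randomisation in practice, one clarifying sentence is enough.

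For anyone already randomised under the overlapping sequence, take as baseline only the wear days before the first message, and add a sensitivity analysis of 6-month MVPA without baseline MVPA as a covariate.

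The cost is a delay of some weeks between consent and first message, a changed trigger in the messaging system, and some loss of participants before randomisation. The sample-size calculation does not change.

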**Enrolment**			
Eligibility screen	✓		
Informed consent	✓		
Randomisation		✓	
**Assessments**			
Demographics		✓	
Physical activity		✓	✓
Dietary intake		✓	✓
BMI^a^ z-score		✓	✓
Waist-to-height ratio		✓	✓
Sleep quality		✓	✓
Quality of life		✓	✓
Self-efficacy		✓	✓
Anxiety		✓	✓
Depression		✓	✓
Psychological distress		✓	✓
Eating disorder risk		✓	✓
Food insecurity		✓	✓
eHealth literacy		✓	✓
Process evaluation			✓

^a^*BMI* Body mass index

### Process measures

The acceptability, utility and engagement with the Health4Me Program will be measured through quantitative and qualitative measures. Firstly, text message data will be extracted from the software system to assess engagement by the number of messages sent, number of responses received, and number of messages ‘bounced’ and undelivered. Secondly, a study-specific user feedback and satisfaction questionnaire will be administered to all participants. It will contain questions on a 5-point Likert scale from strongly agree to strongly disagree regarding acceptability and utility of the program. It will also include open ended questions regarding most and least useful program components and suggestions for program improvement. These responses will be coded thematically, and emerging themes identified. The questionnaire will also ask questions about whether participants used or accessed any other digital health tools to help manage their lifestyle health behaviours during the study. Intervention participants will be invited by text message, email, or phone call to join focus groups after the 6-month follow-up. A minimum of five focus groups will be conducted consecutively until thematic saturation is reached. The focus groups will be conducted via Zoom teleconference and last approximately 45 minutes. Participants will be purposively selected to ensure a mix in terms of age, ethnicity and location are represented to encompass different viewpoints.

### Statistical considerations

For the outcome of MVPA (minutes per day), 312 (156 per group) participants are needed to achieve 90% power to observe the mean difference of 14.8 (control: 42.55 and intervention: 57.36) with standard deviations (SD) of 21.45 for control and 37.79 for intervention and accounting for 30% dropout. A two-sided two-sample unequal-variance t-test was used. The Bonferroni adjusted significance level of 0.025 was used to account for two primary outcomes. To detect a difference in vegetable intake at 6-months, 390 (195 per group) participants will achieve 90% power to detect 13.37% difference in the proportion of appropriate vegetable consumption (control: 4.85% and intervention: 18.22%) and accounting for 30% dropout [61]. The two-sided Z-Test with unpooled variance was used with the significance level of the test is 0.025. Therefore, a sample size of 390 will allow the detection of the change in MVPA or vegetable intake.

All statistical analyses will follow a pre-specified statistical analysis plan guided by our team statistician. Analyses of the primary and secondary outcomes will be conducted according to the intention-to-treat principle. Continuous outcomes at 6-months will be analysed using analysis of covariance (ANCOVA), and categorical outcomes at 6-months will be analysed using log-binomial regression, adjusting for the outcome values at baseline. Planned subgroup analyses will investigate interactions between treatment and subgroups, including categories of age, socioeconomic status and ethnicity, to explore trends for scale up. All tests will be two-sided with a significance level of 0.05. Analyses of the two primary outcomes will be controlled for the family-wise error rate using Holm correction [62]. No multiplicity adjustments will be performed for secondary outcomes as they are exploratory analyses. The analyses will be performed using SAS (V9.4 SAS Institute Inc. Cary NC, USA).

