**Methods:**

Health4Me is a virtual, two-arm, single-blind randomised controlled trial, delivering a 6-month healthy lifestyle text message program with optional health counselling. Recruitment will be through digital advertising and primary care services. In total, 330 adolescents will be randomised 1:1 to intervention or control (usual care) groups. The intervention group will receive 4–5 text messages per week for 6-months. All text messages have been co-designed with adolescents. Messages promote a healthy lifestyle by providing practical information, health tips, motivation and support for behaviour change for physical activity, nutrition, mental health, body image, popular digital media and climate and planetary health. Virtual assessments will occur at baseline and 6-months assessing physical health (physical activity, nutrition, body mass index, sleep), mental health (quality of life, self-efficacy, psychological distress, anxiety, depression, eating disorder risk) and lifestyle outcomes (food insecurity and eHealth literacy).

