## Methods

### Study design

The Health4Me study is a virtual, randomised, controlled, single-blind trial, which delivers a 6-month text message healthy lifestyle program with optional health counselling to 330 healthy adolescents (12–18 years old inclusive) (Fig. 1).

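### The sample-size section requires 390 participants, but the abstract and study design enrol 330; at 330, power for the vegetable primary outcome is about 84%, not 90%

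*Protocol article*

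**What the plan says.** The abstract (Methods) states: "In total, 330 adolescents will be randomised 1:1 to intervention or control (usual care) groups". The Study design section repeats the figure, describing delivery of a "text message healthy lifestyle program with optional health counselling to 330 healthy adolescents".

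The Statistical considerations section works out a size for each of the two primary outcomes at a Bonferroni-adjusted level of 0.025. For MVPA it arrives at 312 (156 per group). For vegetable intake it says that "390 (195 per group) participants will achieve 90% power to detect 13.37% difference in the proportion of appropriate vegetable consumption", with the rates given as "control: 4.85% and intervention: 18.22%) and accounting for 30% dropout". The test is specified: "The two-sided Z-Test with unpooled variance was used with the significance level of the test is 0.025". The section concludes: "Therefore, a sample size of 390 will allow the detection of the change in MVPA or vegetable intake".

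The same section plans a Holm correction across the two primary outcomes in the analysis. The section on data collection and study outcomes says that a significant effect on either primary outcome may count as evidence of efficacy.

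**The concern.** The enrolment target is a basic design fact, and a reader cannot tell whether recruitment stops at 330 or at 390. The figure of 330 cannot be the number left after dropout: the abstract calls it the number randomised, and 390 less 30% is 273.

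The figure of 330 exceeds the 312 derived for MVPA but is 60 short of the 390 derived for vegetable intake. If recruitment stops at 330, one of the two primary outcomes runs below the size the plan says it needs, while the only power printed for it is 90%. A null vegetable result would then be read as stronger evidence of no effect than the trial can give. If 390 is the true target, the abstract and the Study design section misreport the trial.

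**Working it through.** **Inputs** (all from Statistical considerations unless noted)
- Vegetable intake: control 4.85%, intervention 18.22%, difference 13.37 points; two-sided Z-test, unpooled variance, level 0.025, power 90%, dropout 30%.
- MVPA: means 42.55 and 57.36 (difference 14.81, printed as 14.8); SDs 21.45 and 37.79; two-sided unequal-variance t-test, level 0.025, power 90%, dropout 30%.
- Allocation 1:1 (Randomization and blinding).
- Enrolment 330, so 165 per arm (abstract; Study design).

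**Step 1. Reproduce 390.** Completers per arm:

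n = (z₀.₉₈₇₅ + z₀.₉₀)² × [p₁(1−p₁) + p₂(1−p₂)] / (p₂−p₁)²

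= (2.2414 + 1.2816)² × (0.0485×0.9515 + 0.1822×0.8178) / 0.1337²

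= 12.411 × 0.19515 / 0.017876 = 135.5, rounded up to 136.

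With dropout: 136 / 0.7 = 194.3, so 195 per arm and **390** in total. This matches the plan.

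**Step 2. Reproduce 312.** The unequal-variance t-test (noncentral t) gives 89.9% power at 108 completers per arm and 90.2% at 109. So 109 / 0.7 = 155.7, which is 156 per arm and **312** in total. This also matches.

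**Step 3. Power at 330.** Evaluable per arm: 165 × 0.7 = 115.5.

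Vegetable intake: SE = √(0.19515 / 115.5) = 0.04110; 0.1337 / 0.04110 = 3.253; power = Φ(3.253 − 2.241) = **84.4%** (84.2% at 115 per arm, 84.6% at 116).

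| Randomised | Evaluable per arm | Vegetable power at 0.025 | MVPA power at 0.025 |
|---|---|---|---|
| 330 | 115.5 | 84.4% | 91.9% |
| 390 | 136.5 | 90.2% | 95.7% |

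The vegetable shortfall does not depend on the choice of formula. At 115 to 116 per arm, the pooled-variance formula gives 83.0% to 83.3%, and exact enumeration of the unpooled Z-test gives 86.2% to 86.6%.

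**Step 4. Other ways to express the gap.** With control at 4.85%, the difference detectable with 90% power at 0.025 is 13.3 points at 390 and 14.8 points at 330. Holding 90% at 330 needs 136 of 165 per arm to complete. That is dropout of 1 − 136/165 = 17.6%, or about 18%, against the planned 30%.

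**Step 5. Where 330 may come from (inference only).** At an unadjusted 0.05, the Step 1 formula gives (1.9600 + 1.2816)² × 0.19515 / 0.017876 = 114.7, so 115 completers. Then 115 / 0.7 = 164.3, which is 165 per arm and exactly 330. This fits a vegetable calculation without the Bonferroni split. The article does not say so, and the point does not depend on it.

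**The case against.** The strongest objection is that 0.025 is not the level at which vegetable intake will always be tested. Under Holm, if MVPA is significant at 0.025, vegetable intake is tested at 0.05, where power at 330 is 90.2%. With the planned MVPA effect and independent outcomes, overall vegetable power at 330 is 0.844 + 0.919 × (0.902 − 0.844) = 89.7%. The chance of at least one significant primary outcome is 1 − (1 − 0.844)(1 − 0.919) = 98.7% at 330, against 99.6% at 390. Trial-level success is therefore barely affected.

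Those figures are right, and 84% should be labelled as the power at a fixed 0.025. They do not remove the error:
- The plan rests its 90% on 0.025 and never justifies 330 through Holm, so 84% against 90% is the like-for-like comparison. On the Holm basis, 390 gives about 94%, and the gap remains.
- The recovery depends on MVPA succeeding. Either outcome may carry the efficacy claim, and if MVPA shows no effect, vegetable power at 330 is close to 84%.
- Holm cannot explain two different enrolment totals.

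A second objection also has force. The article attaches 90% to 390, never to 330, and does not say which total governs. If 390 governs, there is no power loss, only a wrong figure in two places. The power shortfall is therefore conditional on 330; the contradiction is not.

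**Conclusion.** The point holds. The article states 330 in two places and 390 in its sample-size conclusion, and both cannot be the enrolment target. The figure of 390 is what the stated inputs require.

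If 330 governs, power for vegetable intake is about 84% at two-sided 0.025 instead of 90%, while MVPA keeps about 92%. This assumes the planned rates, 30% dropout, 1:1 allocation and the planning Z-test; it is not the power of the baseline-adjusted log-binomial model named for the analysis. Under Holm the vegetable figure is about 90%, given independence and the full planned MVPA effect.

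This must be corrected, because it concerns the enrolment target and the stated power of a primary outcome.

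**What to change.** Use one total in the abstract, Study design and Statistical considerations.

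- **If 330 is the target**, replace the closing sentence of the sample-size paragraph with: *330 participants (about 115 per arm after 30% dropout) give 92% power for MVPA and 84% for vegetable intake at two-sided 0.025.* The Holm figure may be added with its assumptions: about 90% for vegetable intake if MVPA has its planned effect and the outcomes are independent. The cost is wording and a less favourable stated power.
- **If 390 is the target**, change 330 to 390 in the abstract and Study design. This is a text correction if recruitment is already set at 390. If recruitment is actually set at 330, it means enrolling 60 more participants, which is a real cost and a separate decision.
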